## Abstract

**Background:**

Personal convictions in referral to pain cause misbeliefs in health professionals, which can influence patients who suffer from non-specific chronic low back pain. Likewise, health professionals’ beliefs affect their advice and attitudes towards patients’ treatment, becoming a possible cause of greater disability. The development of educational interventions based on the best scientific evidence in neurophysiology of pain could be a way to provide information and advice to primary care health professionals to change their cognition towards chronic non-specific low back pain. The use of Information and Communication Technologies allows the development of web sites, which might be one of the effective resources to modify misbeliefs and attitudes, in relation to the origin and meaning of non-specific chronic low back pain, of primary care professionals and that may modify their attitudes in patients’ treatment.

**Methods:**

The aim of this project is to identify misbeliefs and attitudes of primary care physicians and nurses about chronic non-specific low back pain to develop a web-based educational tool using different educational formats and gamification techniques. This study has a mixed-method sequential exploratory design. The participants are medical and nursing staff working in primary care centers in the city of Lleida, Spain. For the qualitative phase of this study, the authors will use personal semi-structured interviews. For the quantitative phase the authors will use an experimental study design. Subjects will be randomly allocated using a simple random sample technique. The intervention group will have access to the web site where they will find information related to non-specific chronic low back pain, based on the information obtained in the qualitative phase. The control group will have access to a video explaining the clinical practice guidelines on low back pain.

**Discussion:**

This study has been designed to explore and modify the beliefs and attitudes about chronic low back pain of physicians and nurses working in primary care settings, using a web-based educational tool with different educational formats and gamification techniques. The aim of the educational intervention is to change their knowledge about the origin and meaning of pain, with the result of reducing their misbeliefs and attitudes of fear avoidance.

**Trial registration:**

ClinicalTrials.gov Identifier: NCT02962817. Date of registration: 11/09/2016.

**Electronic supplementary material:**

The online version of this article (10.1186/s12875-019-0919-6) contains supplementary material, which is available to authorized users.

## Background

Low back pain (LBP) is a common musculoskeletal disorder and one of the main reasons why patients attend primary care (PC) centers, which has considerably high socioeconomic impact [1–7]. It is estimated that 60–90% of the adult population will experience LBP at some point in their lives and that between 5 and 10% will develop chronic low back pain (CLBP), defined by the International Association for the Study of Pain (IASP) as the pain that is lasting more than 12 weeks [1, 2, 8, 9]. The prevalence of CLBP increases linearly from the third decade of life to 60 years of age, being more frequent in women [7, 8]. In the context of PC, 80–90% of CLBP cases are considered of non-specific origin, since it is not possible to identify a specific cause that can be associated to the origin of pain [1, 2, 4].

Despite the high prevalence of pain in the population, as well as the burden and impact it poses to the individual, socio-family context and health systems, the IASP concluded that the time dedicated to pain in the education of health professionals (HP) is not enough to achieve effective pain management [10–13]. HP, as a result of their personal beliefs towards pain, often develop misbeliefs that have an impact on clinical approach of patients who suffer from non-specific chronic low back pain (NCLBP) [14]. A systematic review published in 2012 [15] concluded that HP’ beliefs and attitudes toward LBP have a direct influence on patients’ beliefs. They also affect the advice provided to their patients with NCLBP [3, 4, 15]. In addition, HP’ beliefs can alter patient’s interpretation of pain and cause misbeliefs and avoidance behaviors [16]. Several authors rely on the fear-avoidance model to explain the chronic pain process [14, 17, 18]. Patients make a catastrophic interpretation of the situation; they show fear towards physical activity and the development of possible injuries, exacerbating their pain [14, 17, 18]. In fact, fear towards pain is associated with avoidance behaviors, which have a negative impact on NCLBP, which it is strongly associated with disability, physical inactivity, increased drug dependence and overuse of medical services [14]. These avoidance behaviors in patients are reinforced by HP’ strong fear-avoidance beliefs, as they are more likely not to recommend or avoid physical and / or occupational activity and to prescribe passive treatments, sometimes resulting in an increased disability [14]. On the other hand, there is evidence that fear-avoidance beliefs in patients with NCLBP are reduced when they are treated by HP with less misbeliefs, despite the fact they advise patients to go on with their daily activities and occupational activities along with more active treatments, which correlates with a greater degree of functionality [14, 19]. Due to the immediate consequences of fear-avoidance beliefs in relation to health and well being of patients suffering from NCLBP, it may be good for the health system to understand them and to act upon them [14].

The study published by Darlow et al. [15] justifies the use of educational interventions to change the cognitive factors of HP involved in the treatment of NCLBP patients [15]. Several public health interventions have shown that HP’ re-education is effective in changing their cognition towards NCLBP and, consequently, changing their misbeliefs and attitudes towards treatment that may be reflected in those patients [20, 21]. The Societal Impact of Pain [22], a platform supported by the European Federation of IASP Chapters, urges governments and health institutions in the European Union to enhance education in knowledge, prevention, diagnosis and treatment of pain among HP. At present, HP who work in PC centers have clinical practice guidelines (CPG) in order to transfer knowledge to specific recommendations, assisting them in making individual clinical decisions and unifying therapeutic criteria, with the aim of promoting higher quality and welfare equity [23–26]. In Spain, the effectiveness of CPG in PC to change clinical practice is moderated [24]. In 2004, the Catalan Health Institute promoted a CPG for low back spine pathology in adults [27]. These guidelines include teaching material and advice for patients. However, they lack a neurophysiological explanation of the procedures involved in pain [27]. In their systematic review and meta-analysis, Clarke et al. [28] suggest pain neurophysiology (NPP) as a promising educational strategy towards pain and physical, social, and psychological function in patients suffering from NCLBP. It has also been shown to have positive effects on pain perception, disability and catastrophism in patients with chronic conditions [29, 30]. This educational strategy is based on the description of the central and peripheral processing mechanisms of the nociceptive signal and the explanation of how this transmission is modulated by brain processing and influenced by psychosocial factors [16, 31]. The results obtained so far suggest that an educational intervention based on NPP can help HP to conceptualize pain and to modify attitudes towards the treatment of chronic pain in PC [32].

The Information and Communication Technologies (ICT) in PC are a basic tool for patients’ and HP’ empowerment, improving their resolution capacity, efficiency and, consequently, attention quality [33]. Internet is one of the resources that has emerged with ICT development and has changed the way of accessing scientific information. Internet is a great source of information for health care management and an excellent channel of communication for HP. However, the influence it can have in professional practice and, more specifically, in the relationship between HP and patients is not clear [34]. It has been shown that web sites are capable of changing and improving the knowledge of chronic patients, in addition to having a positive impact on their attitudes and behavior [16]. This suggests that web sites could be an effective tool to influence the beliefs and attitudes of HP who work in PC.

Up to now, there is little literature on HP’ misbeliefs and attitudes towards the treatment and management of patients who suffer from NCLBP in PC [17]. Furthering these beliefs and attitudes will provide a greater understanding of the current pain explanatory methods used, as well as their possible impact on NCLBP treatment. HP should be aware of the relevance of these beliefs towards NCLBP approach, due to the fact that the omission of beliefs may be responsible for an increase in the degree of disability in patients.

As a consequence of the exposed previously and based on the results obtained by our research team [35], the objective of this study is to explore the HP’ misbeliefs and attitudes towards the treatment and management of NCLBP in PC to develop a web-based educational tool, based on the NPP.

The hypotheses being tested by our study are:The beliefs and attitudes of fear-avoidance of primary care professionals are held by the lack of knowledge about the origin and meaning of pain.The neurophysiology of pain as an educational intervention using a web site for primary care professionals will change their knowledge about the origin and meaning of pain, with the result of reducing their misbeliefs and attitudes of fear avoidance.

## Methods/design

### Objectives

There are specific objectives for each phase of the study.Phase 1 – Qualitative (QUAL): To identify the misbeliefs and attitudes of primary care professionals towards the treatment of chronic non-specific low back pain in relation to the origin and meaning of pain.Phase 2 - Connecting procedure: To build and develop, using a web site, a biopsychosocial educational intervention based on the results obtained in the qualitative phase.Phase 3 – Quantitative (QUAN):○ Primary outcome. To evaluate the effect of a biopsychosocial educational intervention about fear-avoidance beliefs related to non-specific chronic low back pain, using a web site for primary care health professionals.○ Secondary outcome. To evaluate the effect of a biopsychosocial educational intervention about the knowledge of pain neurophysiology, using a web site for primary care health professionals.

### Study design

To answer the research question a mixed-method sequential exploratory design will be used. This design consists of two stages, where the results of the methodology used in the first phase of the study, in this case QUAL, contribute to the development of the second QUAN phase [36]. In this project, both phases should have the same relevance for the development of an educational tool for PC professionals. The use of a mixed methodology design is justified in this protocol because the integration of both (QUAL and QUAN) methodologies occurs when the data from the QUAL phase contributes to the construction of the educational tool [16].

The process to be followed is:QUAL: Semi-structured personal interviews.QUAN: An experimental study design in which a sample of specialized physicians in family and community care and nurses working in PC health centers, will be randomly assigned to the experimental group and the control group.

### Eligibility criteria

The study population will consist of medical or nursing staff of both genders, working in PC centers in the city of Lleida, Spain.

Inclusion criteria:Professionals registered in the official college of medicine, specialized in family and community medicine or professionals registered in the official college of nursing.Professionals working in any of the PC centers of the city of Lleida.Accept and sign the informed consent form.

### Subjects

The recruitment process will be performed independently in each phase of the study, although the inclusion criteria will be common. To start the recruitment process, the first author will do a presentation of the project in each of the PC centers in the city of Lleida, addressed to the medical and nursing staff. Professionals will be invited to take part in the study and will be provided with a telephone number and an email address through which they can contact the first author.QUAL: Subjects who agree to be part of this phase of the study and who meet the inclusion criteria, will be contacted by the first author to agree on the semi-structured personal interview date. The interviews will take place in the same PC centers during the working day of the professionals to facilitate their participation.QUAN: The recruitment process will start after the end of phase 2. The QUAN phase will consist in a biopsychosocial educational intervention using a web site. The first author will meet individually with HP to ensure that they meet the inclusion criteria and inform them of the study conditions and provide them with the informed consent form. Also, the first author will answer any questions or concerns that may arise and will instruct them on how to access the web site to start their participation in the study.

### Sample size

QUAL: The sample size will be determined by a convenience sampling method to achieve a representative number of HP. To ensure the discursive significance of the study results, the sample will be heterogeneous including doctors and nurses of different genders and age groups. The “snowball” strategy will be used to broaden the interviewed subjects. The final number of subjects will depend on the saturation of the information [37].QUAN: The sample size measurement is based on the study published by Domenech et al. [38] where the results obtained from the Health Care Providers Pain and Impairment Relationship Scale (HC-PAIRS) have been used as reference. Taking into account this study and other similar studies performed in general practitioners and physiotherapists [39–42], a standard deviation of 9 will be considered for the calculation of statistical power. A variation in the HC-PAIRS score of 4.5 (half the standard deviation) will be considered clinically significant. Accepting an alpha risk of 0.05 and a statistical power of 80% to reject the null hypothesis, using a bilateral test, the minimum number of participants will be 63 HP in each group. We assume that the dropout rate in the study will be 20%.

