### Possible limitations

In the elaboration process of the current research protocol, we have detected possible limitations that may discredit the validity and reliability of the results and which are detailed below:

As regards the QUAN phase, one of the possible limitations is that the HP will be aware about the group to which they are assigned and, consequently, the study will be blind only for researchers. Another limitation may be a smaller sample size than expected. A smaller than expected final sample size increases the likelihood of a type II error and limits the internal validity of the study, leading to inconclusive results. However, our results are limited to the HP of the PC centers and should be replicated in randomized control trials with larger sample sizes. A last limitation in this phase could be due to the use of the NPP questionnaire, due to the fact that although it offers valid and reliable results for patients with chronic pain, its psychometric properties have not been investigated in HP [47, 48, 57].

Finally, other limitations may arise from the use of new technologies. In the present project, the educational intervention is based on a web site through which the educational material will be expressed in different formats, such as explanatory videos and 3D images. However, other alternatives and / or formats may have a greater degree of acceptance by the HP in the experimental group [16, 58].

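### The 63 per group contains no allowance for the assumed 20% dropout and no enrolment target is given; if 63 per group are randomised, power is about 70%, not 80%

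*Protocol article*

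**What the plan says.** All the inputs are in the quantitative part of the protocol article's Sample size section:

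- Variability: "a standard deviation of 9 will be considered for the calculation of statistical power".
- Target difference: "A variation in the HC-PAIRS score of 4.5 (half the standard deviation) will be considered clinically significant".
- Error rates: "Accepting an alpha risk of 0.05 and a statistical power of 80% to reject the null hypothesis, using a bilateral test".
- Result and dropout: "the minimum number of participants will be 63 HP in each group. We assume that the dropout rate in the study will be 20"%.

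The Data analysis section names Student's t test for continuous variables. The Data collection section has the variables measured before and after a two-week intervention, with no measurement in between. Under Possible limitations the authors note that "A smaller than expected final sample size increases the likelihood of a type II error". No other sample size or recruitment target for this phase appears in the article.

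**The concern.** The number and the dropout rate stand next to each other but are not connected. A reader cannot tell whether 63 per group is what the trial will randomise or what it needs at the post-test, and only one of these is compatible with the stated 80% power once a fifth of participants are lost.

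This bears on the primary outcome. Someone who leaves before the post-test has a baseline HC-PAIRS score but no follow-up score, and so adds nothing to a t test on the post-test score or on the change. If the trial stops recruiting at the only size the article states, the expected losses alone take it below its stated power for the difference it calls clinically significant.

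**Working it through.** **Inputs.** From Sample size: SD 9, difference 4.5 (standardised difference d = 4.5/9 = 0.5), two-sided alpha 0.05, power 80%, equal group sizes, dropout 20%. From Data analysis: Student's t test.

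**1. Reproduce the stated figure.** Normal approximation, per group:

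n = 2 × (1.960 + 0.842)² / 0.5² = 62.8, rounded up to 63.

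This is the protocol's number, reached with no allowance for loss.

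**2. Could 63 already include the dropout?** It would then need a base of about 50 per group, since 50/0.8 = 62.5, rounded up to 63. With d = 0.5, a base of 50 corresponds to a one-sided 5% test at 80% power, or to a two-sided test at 70% power. The text states "using a bilateral test" and "a statistical power of 80% to reject the null hypothesis", which excludes both. Multiplying by 1.2, a common mistaken inflation, gives 75.6, so 76, which is not 63 either.

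**3. Completers if 63 per group are randomised.** 63 × (1 − 0.20) = 50.4, so about 50 per group.

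**4. Power at each size.** The noncentrality is d × √(n/2): 2.81 at n = 63 and 2.50 at n = 50.

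| Evaluable per group | Normal approximation | t test |
|---|---|---|
| 63 | 80.1% | 79.5% |
| 50.4 | 70.9% | 70.0% |
| 50 | 70.5% | 69.7% |

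**5. Difference detectable with 80% power at 50 per group.** The t-test solution is d = 0.566, and 0.566 × 9 = 5.09, about 5.1 points against the planned 4.5.

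**6. Enrolment needed to keep 63 evaluable.** 63/(1 − 0.20) = 78.75, so 79 per group, 158 in total. Check: 79 × 0.8 = 63.2, with power 80.3% (normal approximation) or 79.6% (t test). Compared with 2 × 63 = 126, this is 32 more participants.

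**7. What baseline adjustment could recover.** Adjusting for baseline multiplies the SD by √(1 − r²), where r is the pre-post correlation. The article gives no value for r, so the values below are assumptions. With 50 completers per group, power for 4.5 points is about 74% at r = 0.3, 77% at r = 0.4 and 82% at r = 0.5.

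**The case against.** The strongest reply is that the wording calls 63 a minimum and follows it at once with a dropout rate. That can be read as 63 evaluable per group, with recruitment to be increased accordingly. On that reading nothing is underpowered and the only gap is an unstated enrolment number. This stands, and it is why the fall to 70% has to be stated as conditional. It does not remove the point, because under either reading the paragraph lacks a figure that follows from its own assumptions.

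Three stronger inferences are tempting, and the article does not support them.

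- *The sample size was miscalculated.* It was not: 63 reproduces exactly from the stated inputs.
- *The number should be 64 because a t test is planned.* The t-test power at 63 is 79.5%. The difference is negligible and nothing rests on it.
- *The authors are blind to the risk of a false negative.* They are not. Possible limitations warns of type II error and inconclusive results if the final sample is smaller than expected. However, that caveat concerns an unexpected shortfall, whereas a 20% loss is what the plan itself expects, so the caveat does not replace applying it.

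It can also be said that a journal article condenses a fuller protocol in which the enrolment target may appear, and that handling of missing outcomes may lie in an analysis plan not shown. Both are possible. But the article chose to print the inputs, the result and the dropout rate together, and as printed they do not agree if 63 is the number to be randomised.

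**Conclusion.** The point holds in this form: the stated 63 per group is the requirement before losses, the 20% dropout has not been applied to it, and no enrolment target is given.

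If 63 per group are randomised, about 50 per group are evaluable and power for 4.5 points is about 70%. The type II risk is then about 30% rather than the planned 20%. If 63 are evaluable, power is about 80% and the missing figure is 79 per group. A reader might infer that the trial is definitely underpowered; the wording does not settle that.

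The 70% figure assumes that the SD of 9 applies to the quantity compared, that dropout is 20% in both groups, that dropouts contribute no post-test score to the analysis, and that the analysis is the unadjusted t test named in the article. Baseline adjustment cannot be used to defend the 80% unless a pre-post correlation is stated: at 50 per group it reaches 80% with r = 0.5 but not with r = 0.3 or 0.4.

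**What to change.** Replace the last two sentences of the quantitative Sample size paragraph with one statement that says whether 63 is randomised or evaluable and makes the figures agree. Either:

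- *About 63 professionals per group will be randomised; with 20% dropout about 50 per group are expected to be evaluable, giving about 70% power for a difference of 4.5 points (80% power for about 5.1 points).* Or:
- *63 evaluable professionals per group are required; allowing for 20% dropout, 79 per group (158 in total) will be randomised.*

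If a baseline-adjusted analysis is to be relied on to support a smaller enrolment, state the assumed pre-post correlation and the power it gives.

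The cost is one sentence. The first option adds no participants but reports a less favourable power. The second adds 32 participants over 126. The article does not say how many eligible professionals work in the city's primary care centres, so the feasibility of the second option is for the investigators to judge.

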### Randomization

Subjects will be randomly allocated to either the intervention or control group using a simple randomization method. The subjects’ randomization will be performed by an external researcher from the Polytechnic School of the University of Lleida with a simple randomization technique using the STATS® program [43]. In order to ensure allocation concealment, the external investigator will provide codes created without a specific order in opaque envelopes that will constitute the randomized passwords to access the web site. The first author will deliver the envelopes with the passwords once the HP have signed the consent form. This will ensure the blinding of the evaluators in relation to the results. Due to the nature of the intervention, it will not be possible to blind the participants.

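### Simple randomisation is valid but leaves the physician/nurse balance to chance; stratifying by profession and adjusting for it would be a cheap gain in precision and credibility

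*Protocol article*

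**What the plan says.** The protocol article, under Randomization, specifies "Subjects will be randomly allocated to either the intervention or control group using a simple randomization method" and repeats that the external researcher does this "with a simple randomization technique using the STATS® program". It mentions no blocks or strata. Under Study design the quantitative phase takes "a sample of specialized physicians in family and community care and nurses working in PC health centers".

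Profession is available in time. Under Eligibility criteria, entry depends on registration with the college of medicine or of nursing. Under Subjects, the first author checks eligibility in person. Under Randomization, the envelope with the password is handed over only after consent. Health discipline is also listed among the baseline variables (Secondary outcome measures).

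Under Data analysis, continuous variables are compared with Student's t test, or a non-parametric test if normality fails. No covariate is named.

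Under Sample size, "a standard deviation of 9 will be considered for the calculation of statistical power" and "A variation in the HC-PAIRS score of 4.5 (half the standard deviation) will be considered clinically significant", giving "the minimum number of participants will be 63 HP in each group". The next sentence assumes 20% dropout without saying whether 63 already allows for it.

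**The concern.** Physicians and nurses differ in training, and the article gives some reason to expect that they may answer differently. It uses separate interview guides for the two professions in the qualitative phase. It describes HC-PAIRS as built for primary care physicians. It takes its standard deviation (SD) from a reference study and from similar studies in general practitioners and physiotherapists, and does not name nurses.

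If profession predicts HC-PAIRS, two things follow in a single trial of this size. A chance difference in the mix of professions moves the unadjusted group difference up or down. In addition, variation between professions stays in the error term of the t test, where it costs power. Both are avoidable with information that the trial already holds before allocation. The allocation part has to be settled before the first envelope is issued; a later analysis plan can add a covariate but cannot change the list.

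**Working it through.** **Inputs from the article.** SD 9, difference 4.5, two-sided alpha 0.05, power 80%, 63 per group, dropout 20%, simple randomisation.

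**Inputs not in the article (assumed).** Physician share 50% (range 30–70%). Physician–nurse gap in HC-PAIRS 4.5 to 9 points. A 1:1 ratio, implied by the equal group sizes.

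**1. The plan's own figure.** n = 2(1.960 + 0.842)² × 9² / 4.5² = 62.8, so 63 per group, with power 0.801. The stated 63 is reproduced (the exact t test gives 63.8, so 64). It is the figure before dropout: 63/0.80 = 78.75, so 79 per group and 158 in total.

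**2. Arm sizes.** With 126 randomised, the size of one arm is Binomial(126, 0.5).

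| Quantity | Result |
|---|---|
| P(exactly 63/63) | 7.1% |
| P(arms differ by 10 or more) | 42% |
| 95% range for one arm | 52 to 74 |
| Power at 63/63 | 0.801 |
| Power averaged over simple randomisation | 0.798 |
| Power at 52/74 | 0.789 |

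The loss is 0.3 percentage points on average and 1.2 at the edge of the 95% range. With 158 randomised, both arms have at least 63 randomised 99.2% of the time.

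**3. Balance of professions.** Physicians per arm and nurses per arm are independent binomials. The difference in physician share has an SD of about √(p(1−p) × 2/63), which is 0.5 × 0.178 = 0.089 at p = 0.5. Exact enumeration at 126:

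| Physician share | SD of difference | P(≥ 10 points) | P(≥ 15 points) | 95% limit |
|---|---|---|---|---|
| 50% | 9.0 points | 25% | 9% | 17.5 points |
| 30% or 70% | 8.2 points | 23% | 7% | 16.2 points |

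At 158 and half physicians, P(≥ 10 points) is 23%.

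**4. Shift in HC-PAIRS.** Shift = gap × difference in share.
- Gap 4.5: 95% limit 4.5 × 0.162 to 4.5 × 0.175 = 0.73 to 0.79 points.
- Gap 9: 95% limit 9 × 0.162 to 9 × 0.175 = 1.46 to 1.58 points.

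The standard error of the group difference is 9 × √(2/63) = 1.60. The 95% limit of the shift is thus about half a standard error at a gap of 4.5 and about one at a gap of 9.

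**5. Variance due to profession.** With a half-and-half split it is 0.25 × gap².
- Gap 4.5: 0.25 × 20.25 = 5.06, which is 6% of the planned variance of 81.
- Gap 9: 0.25 × 81 = 20.25, which is 25% of 81.

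What this means for power at 63 per group depends on what the SD of 9 describes:

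| Meaning of SD 9 | Gap 4.5 | Gap 9 |
|---|---|---|
| Mixed sample: unadjusted → adjusted power | 0.80 → 0.83 (SD 8.71) | 0.80 → 0.90 (SD 7.79) |
| Within one profession: unadjusted power | 0.78 (SD 9.28) | 0.71 (SD 10.06) |
| Within one profession: adjusted power | 0.80 | 0.80 |

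**6. What stratification adds to adjustment.** Adjusting under simple randomisation inflates the variance by about 1/(1 − r²), where r is the correlation between arm and profession. The mean of r² is 1/(126 − 1) = 0.8%. At a 10-point imbalance with half physicians, r² is about 0.01, so the variance rises by about 1%. At 17.5 points the rise is about 3%. Adjustment alone therefore keeps nearly all the precision.

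**The case against.** The strongest reply is that nothing here is wrong. Simple randomisation is unbiased and clearly stated, and the article gives 63 as a minimum for power; it does not promise equal arms. Chance imbalance averages to zero, and if the SD of 9 describes the mixed sample, its effect is already inside the standard error of 1.60. The article gives neither the physician share nor a difference between professions. Separate interview guides show that questions were adapted to each role, not that scores differ. Covariates are commonly left to an analysis plan, which is not shown here. Simple randomisation also cannot be predicted, which has value when the person who recruits also hands over the envelopes.

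Most of this stands. Two stronger readings that a reader might infer are not supported:

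- **That missing 63/63 leaves the trial underpowered.** The loss is 0.3 points of power on average, and 63 is in any case the number before dropout. Blocking would not guarantee 63 completers either.
- **That the comparison is biased or the professions will be unbalanced.** Balance is left to chance, and about three times in four the difference in physician share is under 10 points.

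What the reply does not remove is that the allocation method is fixed in this document, that profession is known in time to use, and that using it costs little.

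**Conclusion.** The point holds as a cheap improvement. The stated methods do not use a variable that the trial already has before allocation and that may well predict the primary outcome. The gain is conditional. If physicians and nurses score alike, nothing of note is lost by the present plan. With a half-and-half split, profession would account for variance equal to about 6% of the planned variance at a 4.5-point gap and 25% at a 9-point gap. Both gaps are assumptions; 9 points is a full planning SD and should be read as the upper end. Most of the gain in precision comes from adjustment. Stratification adds visible balance and therefore credibility. The absence of a covariate in a condensed article is not itself a fault, since an analysis plan may supply one.

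**What to change.** Under Randomization, replace simple randomisation with permuted blocks of randomly varying size, stratified by physician/nurse and generated by the external researcher, with block sizes withheld from the first author. The envelopes need sequence numbers within each profession and must be used in order; the article now describes codes in no specific order. Profession should be taken from the eligibility check, because the personal data form is completed only after the password has been issued.

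Under Data analysis, state that the primary HC-PAIRS comparison includes profession as a covariate.

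The cost is two envelope series in place of one, a little more list preparation, and one sentence in each section. The downside is slight predictability, because participants are not blinded and the first author hands over the envelopes; hidden, varying block sizes limit it. If stratification is not feasible or recruitment has begun, keep the present list and adjust for profession, specified before the outcome data are seen.
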